**Fig. 1 fig0001:**
[figure not shown]
Participants flow.

## Variable

### Independent variables (Predictor)

#### EMG recording

The upper and lower limb muscles of the affected side will be monitored via an 8-channel AD equipment from Delsys, a Trigno™ wireless EMG system (Delsys Inc., Natick, MA, USA; Model number: DSY-DS-T01D-4, 2016; Base Station ID: BID-1437; Sensor dimensions: 27 × 37 × 13 mm). The system will be operated with Lab Chart software (AD Instruments, Version 8.1.30) integrated with Trigno Control Utility (Version 3.6.0). Pre-amplifier gain and analogue bandwidth will follow the manufacturer's default settings.

To ensure correct fixation and avoid electrode and skin impedance, an alcohol-based scrub will be used to cleanse the skin. The recording area will be shaved, where necessary. The sensors will be secured to the skin with manufacturer-provided adhesives to ensure that the sensors will not fall off or move during recording. Sensors will be calibrated before each session by checking baseline noise and electrode impedance as per manufacturer guidelines. sEMG recordings at recruitment will be conducted in a quiet, separate room under standardised clinical conditions. Efforts will be made to minimise electrical interference and movement artefacts by positioning participants comfortably, avoiding proximity to high-power electrical equipment where possible, and ensuring stable wireless signal transmission.

Raw sEMG signals will be acquired at the 1000 Hz sampling frequency and preamplified (0–1.5 mv) using a Delsys electromyography system. Signals will be processed using fourth-order band-pass filtered (20–500 Hz) to reduce motion artefacts and high-frequency noise, followed by full-wave rectification and sampling at 4 kHz and then processed with root mean square (RMS) using 20-ms epochs, corresponding to the instructed movement, excluding transition periods. Crosstalk will be quantified by computing inter-channel correlation during isolated contractions, and artefact rejection will be reported as the proportion of epochs excluded due to excessive noise or signal dropout.

### Electrode placement & task instructions

Surface EMG sensors will be positioned over the muscle belly of the affected upper and lower limb muscles in accordance with SENIAM guidelines and aligned parallel to muscle fiber orientation [29]. For sEMG recording of each muscle, participants will be instructed to perform the corresponding functional movement (eg: elbow flexion movement for the sEMG recording of the biceps brachii muscle) as depicted in Figs. 2& 3. Assistance or gentle resistance will be provided by the therapist as appropriate, depending on the participant's level of paresis. Each contraction will be recorded for a duration of 10 s, and a total of three trials will be obtained. Detailed procedures for electrode placement and recording are provided in Supplementary File 1.

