## Specifications table

**Table utbl0001:** 

Subject area	Neuroscience
**More specific subject area**	Stroke
**Name of your protocol**	Predicting motor recovery using surface electromyography in people with severe motor impairment after stroke: A prospective cohort study protocol
**Reagents/tools**	• Electromyography (Delsys, Trigno wireless EMG 8-channel AD instrument, USA) • Action Research Arm Test Kit
**Experimental design**	Not applicable
**Trial registration**	CTRI/2025/06/088335
**Ethics**	Before the study commencement, all participants will provide written informed consent.
**Value of the Protocol**	• This study explores sEMG as an early biomarker of residual muscle activity, potentially enabling more accurate prediction of motor recovery in people with severe motor impairment than conventional clinical assessments alone. • By identifying patients with residual motor potential despite severe initial motor impairment, the resulting prediction model can guide individualized rehabilitation intensity and goal setting, optimizing functional outcomes. • Few studies have focused on individuals with severe motor deficits in the acute phase. This protocol generates novel evidence that could reshape prognostic practices and inform future research in this high-risk population.

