Despite its advantages, the application of sEMG in early stroke recovery prediction is still unexplored in clinical practice. Currently, the majority of applications focus on biofeedback or rehabilitative monitoring rather than prognostic modelling. The lack of established procedures, limited awareness among clinicians, and differences in signal interpretation may all contribute to this underutilization. Therefore, a thorough examination of the prognostic potential of sEMG is needed, especially during the acute stage of stroke. To bridge this gap, we aimed to develop a prediction model for people with severe motor impairment after stroke, employing surface electromyography to analyse whether the amplitude of muscle activity recorded from upper limb muscles such as anterior deltoid, middle deltoid, long head of biceps brachii, long head of triceps brachii and extensor carpi radialis and lower limb muscles such as tibialis anterior, medial head of gastrocnemius, rectus femoris, and biceps femoris within the first week of stroke could predict upper and lower extremity motor recovery and activity capacity of the upper extremity, postural balance, and walking at 3 months post stroke. These muscles were selected because they represent key proximal and distal muscle groups commonly involved in upper and lower extremity functions, balance and walking functions after stroke [24,25]. We hypothesized that greater sEMG amplitude recorded within the first week post-stroke, reflecting detectable voluntary muscle activity in the absence of visible movement, would be positively associated with upper and lower extremity motor recovery, upper extremity activity capacity, postural balance, and walking ability at 3 months post-stroke.

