## Participants

We will include individuals aged 18–80 years, of any sex, with a first-ever ischemic or haemorrhagic stroke affecting the middle cerebral artery (MCA) or anterior cerebral artery (ACA). Recruitment will occur within seven days of stroke onset, and individuals reporting a Shoulder Abduction and Finger Extension (SAFE) score of <5(0–4) or knee extensor strength of <3/5 on the Medical Research Council (MRC) strength grade within this period will be included. Only those who are medically stable and able to follow simple commands will be included. The exclusion criteria will be individuals with a history of bilateral clinical strokes; those admitted more than seven days after stroke onset; patients who had undergone surgical interventions such as craniotomy or craniectomy; and individuals with pre-existing neurological or musculoskeletal disorders affecting motor functions.

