## Procedure

All patients admitted with acute stroke to the study center during the recruitment period will be consecutively screened within the first week of stroke onset for eligibility. A screening log will be maintained to document the number of patients screened, included, excluded (with reasons), and those who decline participation. Information recorded in the screening log will inform the final participant numbers, as summarised in the study flow diagram (Fig. 1). Patients who fulfil the inclusion criteria will be requested to participate in the study. The measurements will be recorded the next day after the consent for participation. Raw sEMG signals will be collected from the paretic side at two time points—within 7 days and again at 30 days after stroke onset and processed via Lab Chart 8.1.30 software. The raw data (%Maximal Voluntary Contraction) will be normalized by the mean Root Mean Square (RMS) /max RMS X100, which will be used for analysis. Mean RMS will be computed for each 10-second trial during task execution and then averaged across trials. The following clinical assessments will be collected at the 1st and 3rd months after stroke onset: Fugl Meyer Assessment (FMA), Action Research Arm Test (ARAT), Functional Ambulation Category (FAC), 10-meter Walk Test (10MWT), Mini BEST, and Stroke Impact Scale (SIS)Version 3.0. During the hospitalization phase, all the measurements will be performed in a quiet room next to the stroke unit. During follow-up, a recording will be performed at the physiotherapy department. To minimise detection bias, assessors conducting clinical outcome assessments at the 1st and 3rd month follow-ups will be blinded to baseline sEMG measurements. Assessments will be performed by a licensed neurophysiotherapist with formal training in standardised stroke outcome measures. The investigator responsible for sEMG acquisition will be a neurophysiotherapist trained in sEMG recording, will not be involved in outcome assessments, and will remain blinded to all follow-up outcomes.

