## Quality control

### sEMG signal acquisition

Contraction tasks are standardised across participants. Visual inspection will be performed to identify artefacts related to movement, signal dropout, or excessive noise. Trials with a signal-to-noise ratio below 20 dB or excessive artefacts will be rejected. In such cases, recordings will be repeated where feasible; otherwise, affected trials will be excluded from analysis. Baseline noise levels will be checked before each recording session. Crosstalk will be minimised through SENIAM-based electrode placement, alignment with muscle fiber direction, and single-muscle task execution. All sEMG recordings will be conducted by a trained physiotherapist experienced in sEMG acquisition, following a predefined standard operating protocol, and supervised by an investigator team with over 20 years of experience in sEMG and neurorehabilitation research.

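### The sEMG recording task varies with the participant's paresis although the article calls it standardised, so the predictor's link with recovery cannot be separated from baseline severity and therapist help

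*Protocol article*

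**What the plan says.** Under Electrode placement & task instructions, the article fixes the movement for each muscle, the 10-second duration and three trials. It then adds: "Assistance or gentle resistance will be provided by the therapist as appropriate, depending on the participant's level of paresis". Further detail is deferred: "Detailed procedures for electrode placement and recording are provided in Supplementary File 1". That file is not shown.

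Under Quality control (sEMG signal acquisition) it says: "Contraction tasks are standardised across participants". The same section rejects trials with a signal-to-noise ratio below 20 dB. They are repeated where feasible and otherwise left out of the analysis.

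The Background hypothesis treats first-week amplitude as "reflecting detectable voluntary muscle activity in the absence of visible movement". The Specifications table presents sEMG as "potentially enabling more accurate prediction of motor recovery in people with severe motor impairment than conventional clinical assessments alone". The analysed quantity is defined under Procedure: "The raw data (%Maximal Voluntary Contraction) will be normalized by the mean Root Mean Square (RMS) /max RMS X100".

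**The concern.** An assisted attempt and a resisted attempt place different demands on a muscle. If the choice between them follows paresis, the recorded signal partly reflects which condition was used, and that condition reflects a bedside view of severity. Severity is itself expected to predict three-month recovery. The study wants to show that sEMG carries information which clinical examination misses, so a predictor whose recording condition is set by clinical examination undermines that particular claim.

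The exploratory correlation of amplitude with SAFE, offered under sEMG analysis as evidence of convergent validity, is exposed in the same way: a severity-dependent task could produce some of it.

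**Working it through.** The plan gives no figure for this point, so the main check sets its statements side by side.

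1. **Task.** One section makes help or resistance depend on paresis; another says the tasks are the same for everyone. The movement, duration and number of trials are common, but the loading is not.
2. **Room for the condition to vary.** Participants qualify with SAFE 0 to 4, or with "knee extensor strength of <3/5 on the Medical Research Council (MRC) strength grade". Because either criterion suffices, paresis can differ between participants and between the arm and leg of one participant. The condition can therefore differ by person and by muscle.
3. **Whether the condition is captured.** The article does not say that it is coded per trial or entered in the model.
4. **Whether severity is handled.** Baseline motor severity is named only as an auxiliary variable for imputation (Missing data). SAFE appears in the analysis only in the exploratory correlation (sEMG analysis).
5. **Whether sensitivity analyses cover it.** Those under sEMG analysis concern signal processing. The measurement uncertainties listed under Uncertainty, significance and multiplicity are electrode placement, skin preparation and normalisation, not task condition.
6. **Whether normalisation removes it.** Suppose the condition multiplies the signal by a factor k. If mean and maximum come from the same condition, (k × mean)/(k × max) = mean/max, and the factor cancels. If the maximum comes from another condition, k remains. The article does not say which applies, and a non-proportional effect would not cancel in either case.

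**Illustration on assumed values.** None of the inputs below comes from the document. Let severity S (higher = milder) be standard normal and correlate ρ with recovery. The milder half is resisted and the more severe half assisted. Resistance shifts the recorded value by d, in SD units of the sEMG signal. Let b be the correlation that sEMG would have with recovery without any shift, taking that signal as independent of S. The covariance of S with its own median split is 0.399, and the split has variance 0.25. Hence

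observed r = (b + ρ × d × 0.399) / √(1 + d²/4).

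- No sEMG information (b = 0), ρ = 0.6:
  - d = 0.25: 0.060/1.008 = 0.06
  - d = 1: 0.239/1.118 = 0.21
  - d = 2: 0.479/1.414 = 0.34
- Over d = 0.25 to 2 the range is 0.04 to 0.23 for ρ = 0.4 and 0.08 to 0.45 for ρ = 0.8. With severity held fixed, the correlation is 0.
- Real information (b = 0.30), ρ = 0.6:
  - d = +2: (0.300 + 0.479)/1.414 = 0.55
  - d = −1 (resisted recordings give the lower value): (0.300 − 0.239)/1.118 = 0.05
- In that second case the severity-adjusted correlation is 0.3/(0.8 × √(1 + 0.0908d²)), where 0.0908 = 0.25 − 0.399². This is 0.375 with no shift, 0.36 at d = ±1 and 0.32 at d = 2.

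On these assumptions the unadjusted link can be created, inflated or deflated by the task rule, while the severity-adjusted one changes little.

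**The case against.** Several points on the other side have force.

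- **The predictor is a ratio, not raw amplitude.** This stands, and it is why no direction can be claimed. A reader might infer that the bias favours the hypothesis, since resisted and milder participants would show more activity. That follows for raw amplitude only; for the ratio defined under Procedure it is not established.
- **The aim is prediction.** A model can predict well with a confounded predictor if the same assist-or-resist practice is reproduced in use. This stands too. A reader might infer that sEMG carries no information of its own; nothing in the article shows that. The problem is attribution, which the stated hypothesis and the claimed gain over clinical assessment both need.
- **Supplementary File 1 or the standard operating protocol may lay down a graded rule.** That could remove therapist discretion. A fixed rule that still depends on paresis would leave the condition tied to severity.
- **The article does not list its final predictors.** Baseline severity might be among them, but the text gives it no such role.
- **Who chooses the mode.** A reader might assume that the assisting therapist is also the person recording the signal. The article does not say so, and the point does not need it.
- **The month-1 recording.** The same muscle might be assisted in week 1 and resisted later, but no stated analysis uses the change in amplitude, so this is peripheral.
- **The figure of 0.6.** The correlation under Sample size estimation is not tied to severity. Its use above as one value of ρ is an assumption and borrows no support from the plan.

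**Conclusion.** The point holds as a contradiction with a consequence for interpretation. Two sections disagree on whether the recording task is common to all participants. As written, the condition under which the main predictor is measured follows baseline severity, and the article neither records nor models it. An association between early sEMG and recovery cannot then be separated from severity and therapist help.

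The size and sign of the effect cannot be obtained from the document. The ranges above show only what is possible under an assumed half-and-half split, assumed severity–recovery correlations of 0.4 to 0.8 and assumed task shifts of −1 to +2 SD. They are not estimates for this cohort. The matter should be settled before recordings are made, because the mode cannot be recovered afterwards if it was not written down.

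**What to change.** 1. Reconcile the task instructions with the quality-control statement. Define the primary sEMG predictor under one recording condition common to all participants, with mean and maximum RMS both taken under that condition.
2. Record any assisted or resisted trials separately, code the mode for each muscle and trial, and use them only in a sensitivity analysis.
3. Include the baseline severity already collected (SAFE/MRC) in the model and report what sEMG adds beyond it. Adjustment alone would not replace step 1: where the choice is left to the therapist, measured severity may not capture it fully.
4. Amend the 20 dB rule so that a low-signal recording from a very weak muscle is kept as a valid low value. Otherwise a common condition could lead to the weakest participants' recordings being rejected and then imputed.

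The cost is one extra coded field, possibly some extra trials, and one more model term out of the roughly seven anticipated. There will also be more near-zero signals in the weakest muscles.

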**Fig. 2 fig0002:**
[figure not shown]
sEMG recording of middle deltoid.

**Fig. 3 fig0003:**
[figure not shown]
sEMG recording of tibialis anterior.

### Dependent variables (outcome)

Primary outcome measures, including FMA (upper and lower motor assessments), ARAT, and FAC, along with secondary outcome measures such as 10MWT, Mini BEST, and SIS, will be assessed at the 1st and 3rd months post-stroke. The primary endpoint of this study will be motor recovery measured by the FMA score at 3 months post-stroke. The outcome will be analysed on a continuous scale, with clinically meaningful thresholds explored secondarily for dichotomous interpretation where appropriate. In accordance with SRRR guidelines [9], endpoint timing in this study is aligned to biologically informed recovery windows. The additional assessment at the 1st month captures the early subacute phase, which is a critical time point for neural plasticity [[30], [31], [32]]. In contrast, the 3-month time point provides a pragmatic and biologically credible primary endpoint for clinical trials of stroke recovery, consistent with SRRR recommendations.

The FMA is the recommended outcome of upper (FMA-UE) and lower extremity (FMA-LE) motor function in people with stroke. It assesses voluntary movement, coordination, and reflex activity in 33 upper extremity and 17 lower extremity items scored on a scale between 0 and 2 [33].

The ARAT assesses the activity capacity of the upper extremity. It has 19 items ordered in four subscales with hierarchical scoring: grip (4 items), grasp (6 items), pinch (6 items), and gross movement (3 items). ARAT is sensitive to changes in motor recovery and is frequently used both in clinical practice and research to evaluate functional outcomes of the paretic arm [34].

The FAC is a 6-point (scored as 0–5) functional walking assessment of ambulation ability and independence in walking, determining the level of human support needed, regardless of whether assistive devices are used [35].

The 10MWTat a comfortable walking speed is a reliable method for the assessment of walking speed in people with stroke [36]. The 10 MWT will only be assessed in participants able to walk independently (FAC≥3).

The Mini BEST includes evaluation of anticipatory and reactive postural control, sensory orientation, and dynamic gait. It comprises 14 items and has a maximum score of 28 points. Each item will be scored from 0–2, where 0 indicates the lowest and 2 denotes the highest level of function [37].

The Stroke Impact Scale Version 3.0 is a self-report questionnaire that assesses limitations and restrictions in activities and participation following stroke. It includes 59 items, scored on a 5-point Likert scale, evaluating strength, hand function, activities of daily living, mobility, communication, emotion, memory, and participation [38].

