## Missing data

We will make every effort to ensure completeness of follow-up data at respective time points. In cases where data is missing, multiple imputation methods will be employed to facilitate comprehensive data analysis. Missing data in predictors and outcomes will be handled using multiple imputations by chained equations (MICE), under the assumption that data are missing at random. The imputation model will include all candidate predictors, outcome variables, and relevant auxiliary variables (such as age, baseline motor severity, stroke type, and time from stroke onset to assessment) to preserve observed associations. Twenty imputed datasets will be generated, and estimates will be pooled using Rubin’s rules.

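### Walking speed is not measured below FAC 3 by design, yet the missing-data rule imputes missing outcomes with no exception for it

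*Protocol article*

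**What the plan says.** Under Dependent variables (outcome), the protocol article lists "secondary outcome measures such as 10MWT, Mini BEST, and SIS", to be assessed at months 1 and 3. The same section limits one of them: "The 10 MWT will only be assessed in participants able to walk independently (FAC≥3". It describes the grading scale: "The FAC is a 6-point (scored as 0–5) functional walking assessment". Grades 0, 1 and 2 are therefore the group without a walking speed. Table 1 ticks the 10-metre walk test at both visits without repeating the restriction.

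The Missing data section sets a general trigger, "In cases where data is missing, multiple imputation methods will be employed to facilitate comprehensive data analysis", and then the method: "Missing data in predictors and outcomes will be handled using multiple imputations by chained equations (MICE), under the assumption that data are missing at random". It adds that "The imputation model will include all candidate predictors, outcome variables, and relevant auxiliary variables", and that "Twenty imputed datasets will be generated".

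No section gives FAC 0–2 participants a walking-speed value, limits the walking-speed analysis to those tested, or describes a two-part analysis.

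**The concern.** An empty walking-speed cell can arise in two ways. An independent walker may miss the test or the visit; a value then existed and was not recorded. Or the participant may be at FAC 0–2, and the plan itself says no test is done. The imputation rule does not separate the two. Read literally, it fills both.

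The second kind is not a missed measurement, and the data hold nothing from which to impute it. Walking at 3 months is among the stated prediction targets (Background). The cohort is selected for severe impairment, partly through weak knee extension (Participants), so the number of such cells could be appreciable. At stake are the walking-speed summary and its association with early sEMG amplitude. Because all outcomes enter one imputation model, unsupported speeds could also feed into the imputation of other variables.

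**Working it through.** **1. Reading the two rules together.** Among participants seen at a visit, the chance that walking speed is unobserved is 1 at FAC 0, 1 and 2, and 0 at FAC 3, 4 and 5, apart from occasional missed tests. Missingness depends on FAC, which is observed, so missing at random may hold in the formal sense. But the distribution of speed given FAC 0–2 is never seen. The model is fitted at FAC 3–5 and applied at FAC 0–2, with no overlap.

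**2. Sample size used for the illustration.** The plan's formula is n = Z²(1 − r²)/d² = 1.96² × (1 − 0.36)/0.04 = 61.47, stated as 61. With 20% dropout, 61/0.8 = 76.25, stated as 76. Both reproduce and are not disputed here. I use 61.

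**3. How many cells.** The documents do not give the share below FAC 3. For an assumed 20% to 70%, 0.20 × 61 = 12.2 and 0.70 × 61 = 42.7, so about 12 to 43 participants.

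**4. Illustrative simulation.** All inputs in this step are assumptions except n = 61 and the 20 imputations.
- A standard-normal severity covariate x, and latent walking ability correlated 0.7 with x. Ability is cut into FAC grades so that 30%, 50% or 70% reach FAC ≥3.
- Walkers' speed = 0.3 + 0.2 × (FAC − 3) + 0.1x + error with SD 0.15, with a floor of 0.1 m/s.
- Speed is observed only if FAC ≥3. The imputation model contains x and FAC. There were 300 replicates per scenario, and predictive mean matching (PMM) used 5 donors.
- The reference scores FAC 0–2 as 0 m/s. This is a benchmark for comparison, not a claim about the true value.

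| Share with FAC ≥3 | 30% | 50% | 70% |
|---|---|---|---|
| Walkers' mean speed, m/s | 0.585 | 0.561 | 0.538 |
| Mean imputed to FAC 0–2, PMM | 0.354 | 0.280 | 0.239 |
| Mean imputed to FAC 0–2, normal model | −0.131 | −0.146 | −0.159 |
| Cohort mean, reference | 0.177 | 0.276 | 0.378 |
| Cohort mean, PMM | 0.425 | 0.418 | 0.449 |
| Cohort mean, normal model | 0.085 | 0.202 | 0.331 |
| Slope on x, reference | 0.178 | 0.224 | 0.231 |
| Slope on x, PMM | 0.092 | 0.146 | 0.174 |
| Slope on x, normal model | 0.309 | 0.329 | 0.304 |

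**5. Reading the table.** Against the reference, the PMM slope is 0.092/0.178 = 0.52, 0.146/0.224 = 0.65 and 0.174/0.231 = 0.75 of its value. The normal-model slope is 0.309/0.178 = 1.74, 0.329/0.224 = 1.47 and 0.304/0.231 = 1.32 times it. A comparison that does not need the 0 m/s benchmark is one variant against the other on the same data: 0.309/0.092 = 3.4, 0.329/0.146 = 2.3 and 0.304/0.174 = 1.7. The answer depends on an imputation variant that the article does not name, and the observed speeds cannot show which variant is nearer the truth.

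**6. A second assumed set-up, PMM only.** Here latent ability is correlated 0.6 with the predictor, and 30%, 45% or 60% are below FAC 3. The correlation fell from 0.57 to 0.50, 0.55 to 0.46 and 0.51 to 0.39. The direction agrees with PMM above.

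**The case against.** The strongest reply is that the conflict is inferred. A test that is not indicated can be read as not applicable rather than missing. The Missing data section opens by speaking of completeness of follow-up, which suggests planned data that were not obtained. No sentence says that cells below FAC 3 will be filled, and an analysis plan that is not shown could exempt them. That is a fair limit on how firmly the consequence can be stated. It does not remove the point. The article goes beyond a general intention: it fixes the method, the assumption, the model contents and the number of datasets, and it makes no exception. An analyst who followed it as published would impute these cells.

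Several stronger readings are tempting and are not supported:
- *That the association is attenuated.* This holds under predictive mean matching; the normal model reverses it. The article names neither.
- *That FAC below 3 means unable to walk.* The scale grades the human support needed, so some of these participants may walk with help. For the same reason, 0 m/s is a debatable value for them.
- *That most of the cohort is affected.* Eligibility is by arm score or knee extensor strength, so some participants may enter on arm weakness alone.
- *That the same rule would impute outcomes after death.* The article says nothing about deaths, so no finding can rest on it.

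It is also fair to say that the correlation shifts in the second set-up, 0.07, 0.09 and 0.12, are smaller than the protocol's own precision of 0.20, and that FAC, a primary outcome measure recorded without restriction, also serves the walking aim.

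**Conclusion.** The point holds, for a secondary outcome. One stated rule leaves walking speed unmeasured at FAC 0–2, and another, as written, imputes it from data that contain no speed in that group. That such values are unsupported follows from the text and needs no simulation. The size and direction of the error do not follow from the text. They rest on an assumed FAC distribution, assumed speeds, a chosen imputation variant and a 0 m/s reference. Under those assumptions the slope ranged from about half to about 1.7 times the reference. The primary Fugl-Meyer endpoint is not directly affected; spill-over through the shared imputation model is possible and was not quantified.

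**What to change.** In the Missing data section, state that a 10-metre walk test not done because FAC is below 3 is not missing data and is not imputed. Keep chained-equation imputation of walking speed for an eligible participant whose test or visit was missed. Where FAC itself is unknown because the visit was missed, impute FAC first, and speed only in those imputed datasets in which FAC is 3 or more. Let FAC carry the walking information when other variables are imputed.

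Then name an analysis that needs no invented speeds. Two options are:
- analyse speed among those tested, with the proportion below FAC 3 reported alongside; or
- use a two-part or rank-based analysis in which FAC below 3 is the lowest category.

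The cost is a few sentences. Data collection and sample size do not change. The downside is small: the walking-speed result then applies to independent walkers only, or the model for this secondary outcome is slightly more complex.
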